## Abstract

**Background:**

Genetic counseling for hereditary breast or colon cancer has implications for both counselees and their relatives. Although counselees are encouraged by genetic counselors to disclose genetic cancer risk information, they do not always share this information with their at-risk relatives. Reasons for not informing relatives may be generally categorized as a lack of knowledge, motivation and/or self-efficacy. Presented here is the protocol of a randomized controlled trial that aims to establish the effectiveness of an intervention focused on supporting counselees in their disclosure of genetic cancer information to their relatives.

**Methods/Design:**

A multicenter randomized controlled trial with parallel group design will be used to compare the effects of an additional telephone counseling session performed by psychosocial workers to enhance the disclosure of genetic cancer information to at-risk relatives (intervention group) with a control group of standard care. Consecutive index patients with relatives at risk for hereditary or familial breast and/or ovarian cancer or colon cancer, are randomly assigned (block size: 8; 1:1 allocation ratio) to the intervention (n = 132) or control group (n = 132, standard care). Primary outcomes are counselees’ knowledge, motivation and self-efficacy regarding informing their relatives.

**Discussion:**

This intervention may prove important in supporting counselees to disclose hereditary and/or familial cancer risk information to at-risk relatives and may enable more at-risk relatives to make a well-informed decision regarding genetic services and/or screening.

**Trial registration:**

This trial is registered in the Netherlands National Trial Register (NTR) with trial ID number NTR3745.

## Background

Identification of hereditary or familial breast or colorectal cancer risks has implications not only for counselees but also for their relatives. Knowledge of genetic test results in families is important to individualize recommendations for risk reduction for at-risk relatives (that is, DNA testing, regular breast or colon screening and/or (prophylactic) surgery) [1-3].

According to international [4] and Dutch [5] guidelines, genetic counselors encourage counselees to inform at-risk relatives about their genetic test result and the availability of surveillance options. Thereby, genetic counselors face the challenge of encouraging counselees to inform their relatives to enable them to make an informed decision about their own health, while also supporting counselees’ autonomy [6]. The counselees’ wish not to inform relatives has to be respected, and relatives’ wish not to know has to be taken into account since they may consider the information to be an invasion of their own privacy [7].

Although counselees report that they generally feel responsible to disclose genetic risk information to relatives [8-10], they do not always succeed in correctly informing all relevant relatives [11-15]. As a result, relatives may lack the opportunity to make a well-informed decision about whether or not to pursue genetic counseling, DNA testing and/or surveillance activities [4,16].

To date, several (mostly qualitative studies) have addressed counselees’ barriers to informing their relatives [14,15,17,18]. Barriers may be categorized as lack of knowledge, lack of motivation, and lack of self-efficacy. When counselees have a lack of knowledge, their understanding of family members that ought to be informed may not be sufficient [18,19]; moreover, insufficient knowledge may lead to incorrect disclosure [20]. A lack of motivation, may be due to the desire to protect the relative or oneself, for example, from negative reactions by the relative [10]. Moreover, counselees may consider a relative to be too emotionally fragile to burden them with genetic cancer information [19], or relatives may be perceived as not mature enough to understand the information [21] or as too old and, therefore, no longer in a high-risk life stage [14]. A lack of self-efficacy may lead to counselees feeling unable to inform their relatives. The counselee does not deliberately withhold information but may feel insecure about correctly disclosing the complex or burdensome information [22].

As a result of feeling responsible about the need to inform relatives, but at the same time facing several barriers, counselees may experience their messenger role as a burden [23]. Indeed, cancer genetic counselees report a need in genetic counseling for information and support in communicating the genetic information to others [24,25]. Counselees also express that their lack of confidence in disseminating information may be improved by more professional backup [7].

To address the need to support counselees and the call for an intervention by others [26,27], various interventions have been developed to improve family communication about genetic testing and screening options [28-31]. These interventions mainly comprise enhanced information [29,31] or communication skills training [28,31] for counselees. However, no effects on facilitating the family communication process were found, except for improving counselees’ satisfaction [31]. One study developed a counseling intervention to support counselees in communicating genetic information to at-risk relatives; this intervention comprised the use of a pedigree chart (for example, a document to record medical family history) to explicitly identify at-risk relatives, a follow-up letter stressing the importance of family disclosure, and two follow-up telephone calls during which it was documented which relatives had been informed and offering guidance about how to approach relatives [32]. Investigation of the effectiveness of this intervention indicated that the proportion of at-risk relatives using genetic services was larger in the intervention group (61%) compared with the control group (36%); however, this latter study had a cohort design (instead of a randomized design) thereby limiting the possibility to draw firm conclusions [32].

This paper describes the design of a randomized controlled trial (RCT) for investigating the effectiveness of an intervention based on the principles of Motivational Interviewing (MI) [31]. MI is a client-centered counseling style that helps individuals change health-related behavior, such as sharing hereditary cancer risk information with relatives. We consider that this client-centered but directive counseling style of MI is well suited for counselors, since they have to discuss family communication with counselees while at the same time respecting counselees’ autonomy.

The intervention, consisting of an additional telephone counseling session conducted by psychosocial workers, aims to support counselees in disclosing hereditary or familial cancer risk information to at-risk relatives. This paper presents details of the design of this RCT, guided by the CONSORT checklist [33].

This RCT (registered in the Dutch National Trial Register: NTR3745) aims to test the following hypotheses:

**Hypothesis 1** - The intervention will increase counselees’ knowledge, motivation and self-efficacy with regard to informing relatives about their hereditary or familial cancer risk, as compared with counselees who receive standard care.

**Hypothesis 2** - The intervention will lead to more at-risk relatives being informed by counselees; increased knowledge among relatives about hereditary/familial cancer and preventive measures; and increased intention of informed relatives to engage in genetic counseling, testing and/or preventive measures, compared with the standard care condition.

**Hypothesis 3** - The intervention will be positively evaluated by counselees and psychosocial workers.

## Methods/Design

### Trial design

The study comprises a multicenter RCT with a parallel group design, comparing the effects of an additional telephonic counseling session aimed at supporting counselees in informing their at-risk relatives (intervention group), with a control condition of standard care only. Participating counselees will complete a questionnaire at three moments:

1. Pre-intervention (T1), after receiving a summary letter from the genetic counselor,

2. Post-intervention (T2), immediately following the intervention, or -in standard care - at the same time (about 4 weeks after T1),

3. Follow-up (T3) at 4 months after T1.

At T2 counselees are telephoned to complete items regarding their insight as to who to inform and their knowledge on surveillance measures; the rationale behind the telephone intervention is that these items are too complex to complete alone. At T3, participants will invite at-risk relatives to also complete a questionnaire (Figure 1).

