### Primary outcome measures

At T2 the primary outcomes will be assessed by questionnaire (and partly by telephone) using specific instruments (Figure 1). Details on the development and psychometric properties of the outcome measures will be published separately.

Knowledge will comprise counselees’:

1. Insight into which relatives need to be informed, as indicated by a percentage ‘correct knowledge’ specifying the relative number of family members that need to be informed, correctly remembered by the counselee (range 0 to 100).

2. Knowledge about surveillance measures for relatives, as indicated by the percentage ‘correct knowledge about surveillance options’ that indicates how many screening options for relatives (1 to 6), are correctly remembered by the counselee (range 0 to 100).

3. Risk perception, as measured with two items: perceived lifetime breast and/or ovarian or colon cancer risk in percentages, and perceived breast and/or ovarian or colon cancer risk as compared with the average Dutch woman or person (5-point Likert scale: 1 = very strongly lowered, 5 = very strongly heightened).

4. General knowledge about hereditary breast or colon cancer, which includes six items developed by Pieterse *et al*. [42] based on the work of Claes *et al*. [14]. All items are presented as statements with three response categories (‘Correct’, ‘Incorrect’, or ‘I do not know’). A higher score indicates more knowledge about hereditary cancer.

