### Blinding

The informed consent procedure to postpone information enables a blind design for participants in the control group. Participants in the intervention group will be masked for the exact study objective to avoid biased outcome measures. Psychosocial workers and research assistants who collect data cannot be blinded. At T2, research assistants will obtain outcome measures by telephone. To ensure that the outcomes are obtained as objectively as possible, a telephone script has been developed to minimize individual differences between research assistants. Also, to minimize additional bias, data entry is performed by someone other than the person who performs the analyses.

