### Data analysis

All analyses will be based on the intention-to-treat principle. Assuming random dropout, incomplete data will be imputed using data of the control group, that is, standard care.

*Hypothesis 1:* Multilevel analysis will be used to investigate whether the intervention increases counselees’ knowledge, motivation and self-efficacy as compared with the control group. Effects of the intervention will be investigated on each of the seven outcome variables separately. The three moments of measurement (T1, T2, T3) will be treated as nested within counselees.

*Hypothesis 2:* Multilevel analysis will also be used to investigate whether the intervention increases: the number of correctly informed relatives; relatives’ knowledge about hereditary/familial cancer and preventive measures; and relatives’ intention to engage in genetic counseling. For this, the relatives will be treated as nested within counselees and counselees will be treated as nested within physicians.

*Hypothesis 3:* To investigate how counselees and psychosocial workers evaluate the intervention, descriptives and frequencies will be calculated to present counselees’ and psychosocial workers’ evaluation of the intervention.

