Second, similarity of the two study arms is not guaranteed since participants in the intervention arm receive more attention than the controls. Therefore, it is difficult to precisely define the effective components of the intervention. Also, a third study arm, comprising a condition with only a telephone call was considered to be too ambitious given the additional number participants required. However, to gain insight into the effective components of the intervention, we aim to compare the group of counselees who only needed the first phase of the intervention (that is, systematically exploring disclosure of genetic cancer information to at-risk relatives) with those who also received the second phase of the intervention (that is, building motivation, self-efficacy, brainstorming).

Moreover, pilot work revealed the complexity of gaining reliable insight into the counselees’ knowledge regarding which relatives to inform and what to tell relatives by asking them to complete questionnaires. Therefore, completion of the questionnaire after the intervention (T2) is done (in part) by telephone to ensure that the counselees understand the items correctly. This telephone call, performed by the researchers, might be seen as an intervention on its own, since counselees are asked about family communication in a systematic way. For that reason, the telephone call is scripted and standardized as far as possible.

Finally, studies in which relatives are invited to participate, including the present study, have some limitations. Medical-ethical regulations preclude geneticist/researchers from directly approaching the relatives of counselees. Therefore, we ask the participating counselees to invite their relatives to participate; this may cause some selection bias since only those relatives can be invited who have been correctly informed by the counselee. To prevent this bias, we use the pedigree of the participant, and for each individual relative, we systematically ask whether this relative may be invited or not.

This paper is the first of a series that will outline the development and testing of an intervention to enhance family communication about hereditary or familial cancer risks; here we describe the study protocol of the RCT. Additional papers will describe the development and psychometric properties of the outcome measures, pilot testing, and the outcomes of the trial.

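### Two primary outcomes are taken by telephone at T2 by callers declared impossible to blind, though nothing described requires them to know the arm; whether these items exist at T1 and T3 is also left open

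*Protocol article*

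**What the plan says.** **Collection.** Counselees fill in a questionnaire at T1, T2 and T3: "Participating counselees will complete a questionnaire at three moments". At T2, "At T2 counselees are telephoned to complete items regarding their insight as to who to inform and their knowledge on surveillance measures", because "these items are too complex to complete alone". Primary outcome measures repeats this: "At T2 the primary outcomes will be assessed by questionnaire (and partly by telephone) using specific instruments". The Discussion gives the background: "pilot work revealed the complexity of gaining reliable insight into the counselees’ knowledge regarding which relatives to inform" by questionnaire. T1 is web-based or on paper (Recruitment and informed consent). No telephone contact for outcomes is described at T1 or T3.

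**Blinding.** "Psychosocial workers and research assistants who collect data cannot be blinded". Research assistants obtain the T2 telephone outcomes. Two safeguards are given: a script intended to reduce differences between assistants, and data entry by someone other than the analyst.

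**Analysis and power.** "Effects of the intervention will be investigated on each of the seven outcome variables separately", with T1, T2 and T3 nested within counselees (Data analysis). The Sample size section bases 132 per group on 80% power for the group-by-time interaction, with a correlation of 0.7 and no difference in primary outcomes at T1.

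**The concern.** Both telephoned items count what the counselee correctly recalls: which relatives to inform, and which surveillance options apply. A caller who knows the arm can prompt more, wait longer or accept a looser answer. The same content is checked in step 2 of the intervention, so these are outcomes on which a caller could expect the arms to differ. The trial uses postponed-information consent to keep controls unaware that others receive extra care, and an assessor who knows the arm gives up part of that protection.

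The second issue is whether the analysis matches the data. By the protocol's own reasoning, self-completed T1 and T3 values of these items would be doubtful, yet the model and the power calculation need all three moments. If the items exist only at T2, neither the group-by-time model nor its 80% applies to them.

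**Working it through.** **Blinding: the passages side by side**

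1. Who delivers the session: psychosocial workers (Intervention group). They necessarily know the arm.
2. Who makes the T2 call: research assistants (Blinding). No passage gives them a part in the session.
3. Who is called at T2: counselees in both arms (Trial design).
4. What the script does: it standardises assistants against each other. An assistant using it may still know the arm.
5. What separate data entry does: it separates entry from analysis, after the answer has been obtained.
6. Where the arm could leak: the call seeking consent to the intervention, made only in that arm (its caller is not named); the timing of T2, which in that arm follows the session; and the counselee's own remarks.

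Items 1 to 3 show no task for which the T2 caller needs the allocation. Items 4 and 5 do not hide it. Item 6 limits what can be achieved but does not make blinding impossible.

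**Power: reproducing the stated figures**

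Inputs from Sample size: effect 0.5 against 0.2, so a difference of 0.3 SD at T2; none at T1; correlation 0.7; alpha 0.05; n = 132 per arm. Assumed here: SD 1, the 0.3 persists to T3, first-order autoregressive correlation (0.7, 0.7, 0.49).

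- Group differences d = (0, 0.3, 0.3), mean 0.2; sum of squares about the mean = 0.04 + 0.01 + 0.01 = 0.06.
- The correlation matrix sums to 3 + 2(0.7 + 0.7 + 0.49) = 6.78. Within-subject error = (3 − 6.78/3)/2 = 0.37.
- Interaction noncentrality = (132/2) × 0.06/0.37 = 10.7. With the Geisser-Greenhouse correction (epsilon 0.875), power = 80.2%, and 132 is the smallest n reaching 80%.
- Group effect: noncentrality = 66 × 0.2²/(6.78/9) = 3.50, power 46.2% (stated 46%).
- Time effect: above 99% (stated 99%).
- Recruitment: 660 × 0.5 × 0.8 = 264, so 132 per arm is net of dropout.

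The stated figures are therefore sound for an outcome measured at all three moments with correlation 0.7.

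**Power under other collection schedules** (two-sided 5%, 132 per arm, 0.3 SD)

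| What exists for the two items | Calculation | Power |
|---|---|---|
| T2 only | SE = √(2/132) = 0.123; Φ(0.3/0.123 − 1.96) | 68.3% (175 per arm for 80%) |
| T2 and T3, no T1, correlation 0.7 | SD of mean = √(1.7/2) = 0.922 | 75.3% (149 per arm) |
| All three, correlation 0.7 | as above | 80.2% |
| All three, correlation 0.6 / 0.5 / 0.3 (assumed) | same model | 69.6% / 61.4% / 50.4% |

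T2 comparison with T1 as a covariate, SE = √[(2/132)(1 − r²)]: 92.7% at r = 0.7, 80.4% at r = 0.5, 72.4% at r = 0.3 (the last two correlations are assumed).

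**The case against.** **On blinding.** The protocol is open about the limitation and standardises the call. T2 in the intervention arm follows the session, so timing may hint at the arm, and some counselees will mention the session. All of this stands, and it means concealment will be incomplete. It does not show that the assistants must be told the arm.

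A reader might also infer that the caller scores answers against the pedigree. The text does not say so: pedigrees are mentioned for the psychosocial workers and for inviting relatives. Who scores the T2 answers is not stated.

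**On the model and power.** A reader might conclude outright that the T1 to T3 model cannot be fitted and that 80% is wrong for these two items. The documents do not support that. No passage says the items are absent at T1 or T3; the data-collection flowchart (Figure 1) is not shown; Sample size makes an assumption about primary outcomes at T1, which suggests T1 values exist; the mode at T3 is not given; and the stated figures reproduce. A change of mode common to both arms is confounded with time but does not by itself bias the group-by-time contrast. The lower correlations in the table are assumptions.

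A reader might also take the 20% dropout off 132 and quote about 59% for roughly 106 per arm. The Sample size arithmetic has already allowed for dropout, so 68% is the figure for a T2-only outcome.

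**Conclusion.** The blinding point holds as stated. Two of seven primary variables are obtained by callers declared impossible to blind, the stated safeguards do not conceal allocation, and no reason for the callers to know the arm is given. The size and direction of any bias cannot be calculated from the document.

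The analysis point is secondary and conditional. If the two items are collected only at T2, the three-moment model cannot be fitted to them and power is about 68% at 132 per arm, assuming a 0.3 SD difference and a two-sided 5% test. If they are collected at all three moments with correlation 0.7, the stated 80% stands. The visible text does not settle which applies, although its own reason for telephoning makes the question a fair one.

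**What to change.** **Blinding.** For T2, replace the statement that research assistants cannot be blinded with three arrangements:
- call lists that omit allocation;
- T2 calls not made by whoever made the intervention-consent call;
- answers scored by existing staff without sight of the arm.

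Do not add a script line asking counselees not to mention extra contacts. Controls would hear it too, and it could reveal what the postponed-information consent conceals.

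**Analysis.** State whether, and in what mode, the two items are collected at T1 and T3.
- If only at T2: make the primary analysis for these two outcomes the T2 between-arm comparison, adjusted for the randomisation strata, and restate power as about 68% at 132 per arm for 0.3 SD.
- If T1 values exist: use T1 as a covariate in that comparison; the stated 80% need not change if the 0.7 correlation holds.

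**Cost.** Wording and a reallocation of calls and scoring among existing staff; no additional participants. The downsides are that some counselees will still reveal their arm, call timing may hint at it, and the stated power for two outcomes may fall.

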**Figure 1 F1:**
[figure not shown]
Flowchart of the randomization procedure, intervention and data collection.

### Participants

Consecutive counselees visiting the department of Clinical Genetics of three university hospitals in the Netherlands will be recruited. The sample comprises the following groups of counselees: those with conclusive test results (a pathogenic mutation has been found), those with an inconclusive test result, and those in whom DNA testing is not possible. For the latter two groups there is an increased cancer risk based on family history.

#### Inclusion criteria

Participants will be counselees who: 1) are the first in their family to visit the Clinical Genetics department for hereditary or familial colon or breast and/or ovarian cancer (referred to as: index patients); 2) have at least one relative at increased risk, that is, eligible for genetic testing and/or surveillance; 3) are aged ≥ 18 years, and 4) are able to read/write Dutch.

